## Abstract

**Background:**

Falls in older people continue to be a major public health issue in industrialized countries. Extensive research into falls prevention has identified exercise as a proven fall prevention strategy. However, despite over a decade of promoting physical activity, hospitalisation rates due to falls injuries in older people are still increasing. This could be because efforts to increase physical activity amongst older people have been unsuccessful, or the physical activity that older people engage in is insufficient and/or inappropriate. The majority of older people choose walking as their predominant form of exercise. While walking has been shown to lower the risk of many chronic diseases its role in falls prevention remains unclear. This paper outlines the methodology of a study whose aims are to determine: if a home-based walking intervention will reduce the falls rate among healthy but inactive community-dwelling older adults (65 + years) compared to no intervention (usual activity) and; whether such an intervention can improve risk factors for falls, such as balance, strength and reaction time.

**Methods/Design:**

This study uses a randomised controlled trial design.

A total of 484 older people exercising less than 120 minutes per week will be recruited through the community and health care referrals throughout Sydney and neighboring regions. All participants are randomised into either the self-managed walking program group or the health-education waiting list group using a block randomization scheme.

Outcome measures include prospective falls and falls injuries, quality of life, and physical activity levels. A subset of participants (n = 194) will also receive physical performance assessments comprising of tests of dynamic balance, strength, reaction time and lower limb functional status.

**Discussion:**

Certain types of physical activity can reduce the risk of falls. As walking is already the most popular physical activity amongst older people, if walking is shown to reduce falls the public health implications could be enormous. Conversely, if walking does not reduce falls in older people, or even puts older people at greater risk, then health resources targeting falls prevention need to be invested elsewhere.

**Trial Registration:**

Australia and New Zealand Clinical Trials Register (ANZCTR): ACTRN12610000380099

## Background

Falls in older people continue to be a major public health issue in industrialized countries [1]. Injuries resulting from falls are a leading cause of death and hospitalisation in people aged 65 years and over [2]. Falls can also lead to poor quality of life, loss of independence, and nursing home admission [3].

In New South Wales (NSW), the most populous state in Australia, there is already a heavy economic burden on the health system due to the cost of falls in older people. In 2006/07, the total lifetime cost of fall-related injury among older people in NSW was estimated at $558 million [4]. As in other industrialized countries and the rest of Australia, the NSW population is ageing and, based on demographic change alone, the cost to the health system of fall-related injuries is predicted to triple by 2050 [5].

Strategies to prevent falls among older people have been extensively researched over the past few decades resulting in a strong evidence-base for effective intervention in this area. Exercise is now recognized as a proven stand-alone fall prevention strategy [6,7] and is currently part of the evidenced-based recommendations in the UK-USA,[8] and Australia [9].

Despite over a decade of promoting physical activity, hospitalisation rates due to falls injuries in older people are still increasing [10,11]. This could be because efforts to increase physical activity amongst older people have been unsuccessful (or are unsuccessful amongst those most at risk of falling), or the physical activity that older people engage in is insufficient and/or inappropriate for falls prevention.

Various modalities of exercise have been tested in relation to their efficacy in preventing falls. In a recent meta-analysis of 54 physical activity-based trials studies it was found that most (64%) of the variability between trials was explained by three program-related features: a higher dose of exercise (≥ 50 hours over the entire trial period), the inclusion of balance challenging training (i.e., activity that moves the centre of mass while narrowing of the base of support and minimizing upper limb support), and not including a walking component in the program [7]. The latter finding raises an important public health issue given that the majority of older people choose walking as their predominant form of exercise [12,13].

Walking can substantially lower the risk of many chronic diseases and ameliorate the health care costs of this population [14] yet, given the above findings, its role in falls prevention remains unclear. One study found that people aged 75 years or older who were randomised to an individually prescribed home-based exercise program, which included walking, reported fewer falls than those randomised to a control group [15]. However, another study that examined the effects of walking on bone mass density in post-menopausal women found that participants in a brisk walking group had higher fall rates compared to the control group [16]. It is possible that increased walking by older adults results in greater exposure to the risk of falling (e.g., environmental hazards). This is consistent with studies that found the highest proportion of outdoor falls occur while walking [17,18].

Further, the potential of walking to improve risk factors of falls, such as balance, is also unclear. A 15-week walking program showed no significant effect on balance among sedentary, post-menopausal women [19]. On the other hand, a study which compared three different balance training programs, including walking, found that all three programs improved dynamic balance, but walking had a bigger impact on static balance [20].

Given the inconsistent evidence on the benefits of walking in the area of falls prevention, the aims of this study are to determine:

i. if a home-based walking intervention will reduce the falls rates among healthy but inactive community-dwelling older adults (65 + years) compared to no intervention (usual activity) and,

ii. whether such an intervention can improve risk factors for falls, such as balance, strength and reaction time.

## Methods

### Design

The design of this study is a randomized controlled trial (see Figure 1). Ethical approval to conduct this trial has been granted by the Research Ethics Review Committee of the Sydney South West Area Health Service-Eastern Zone (X08-0279 & HREC/08/RPAH/477). The study is registered with the Australian New Zealand Clinical Trials Registry (ACTRN12610000380099).

**Figure 1 F1:**
[figure not shown]
**Flowchart of participant recruitment**.

#### Participants

Sedentary, independent, community-dwelling people aged 65 years and over will be eligible to be recruited into this study. A person will be considered sedentary if they are participating, on average, in less than three moderate intensity sessions of physical activity or equivalent per week, totaling no more than 120 minutes [21]. Eligible participants will be also: able to speak and read English proficiently; walk unaided or with minimal assistance (e.g. walking stick) for at least 50 meters; free of any cognitive impairment or neurological conditions limiting their full participation in the study (e.g. dementia, debilitating arthritis, severe vision impairment); otherwise able to participate in physical activity or an exercise program unsupervised, and; not participating or enrolled in any other study.

#### Recruitment and randomization

Participants will be recruited using a variety of methods which include paid advertisements and editorials in community newspapers, use of elector information, distribution of flyers and other printed material promoting the study and through recommendations by study participants. Potential participants will call a research assistant who then screens them for eligibility as well as collecting basic demographic information. A study information kit, which includes a participant information sheet, an ethics consent form, and a medical clearance form (which asks participants to record any medical conditions and medications they are taking for these conditions), will then be posted. On completion and return of the consent and medical clearance forms a baseline interview will be conducted.

After completing the baseline interview participants will be asked if they would be willing to undergo a set of physical performance tests in their own home. Participants choosing not to be a part of the physical performance tests will be randomised immediately after the baseline interview is completed. The sub-set of participants agreeing to undergo physical performance tests will be randomised after the physical performance measures have been completed.

Participants will be randomised into either the self-managed walking group program or the health-education waiting list using sealed opaque envelopes prepared according to a block randomization scheme. The chief investigator (AV) developed the randomization scheme using a table of random numbers and will not be involved in recruitment or data collection. Participants will be assigned to groups after the baseline interview or, for a sub sample of participants, when the physical performance measures are completed. Participants will obviously not be blinded to group allocation. There will be no information about individual participant's group allocation revealed to research assistants during the follow-up interview until the last set of questions which are related to evaluation of the program.

#### Intervention

Participants randomised to the intervention group will receive a self-managed, progressive 'brisk' walking program. This consists of a series of three manuals and telephone coaching conducted over 12-months (48 weeks). The program will start at a level appropriate for sedentary individuals, and will be tailored to accommodate each individual's baseline physical activity levels. The program will progressively guide participants to increase their frequency and duration of walking until participants achieve a minimum of 150 minutes of 'brisk' walking (defined as walking at a pace where you can just barely hold a conversation while walking) per week (for example, over 5 days/week of 30 minute walks or more). This level of intensity is defined as a moderate walking pace which will maintain a safe yet beneficial level of activity for inactive older adults [19,22].

The walking manuals and the telephone support target five constructs from social cognitive theory. These constructs include: knowledge (i.e., walking for health benefits, walking recommendations, safety issues), behavioral skills (i.e., how to use pedometers for feedback, assessment of walking efforts), goal-directed behaviour and self-regulation (i.e., defining short-term achievable goals for each week and for each phase, recording of walks/steps), outcome expectations (i.e., recognizing personal benefits from the walking regimen) and reinforcement (i.e., rewards for reaching goals) [23,24]. The walking manuals have been designed to correspond to three intervention phases aimed towards building an exercise routine for sedentary adults.

The first phase of the walking manual (Walking Manual: Volume One) is the adoption phase, of 12 weeks duration, which focuses on accumulating walking time through a gradual increase of the frequency (weeks 1-4 of the program) and the duration (weeks 5-12) of walking according to the participants ability. Phase two (Walking Manual: Volume Two) is a transition phase (weeks 13-24), which focuses on increasing walking intensity to a brisk pace. The third phase (weeks 25-48) is the maintenance phase which focuses on strategies to maintain the level of walking reached in the previous phase [25]. The maintenance phase also includes strategies to manage setbacks and relapses. Participants receive telephone counseling at the beginning and mid-point for each phase of the program; a total of eight calls. Figure 2 is a flowchart of how participants progress through the study.

**Figure 2 F2:**
[figure not shown]
**Flowchart of participants through the study**.

Intervention group participants will record the duration and frequency of walking, on their falls calendar. Although not a compulsory part of the program, these participants will also be encouraged to use a pedometer mainly as a motivational tool to encourage participants to keep walking. Participants can do this by comparing how many steps they have taken during their walking program towards a previously set goal. The pedometer used will be the Yamax Digiwalker SW-200 pedometer, which has been successfully used to promote walking in community dwelling adults [26].

The control group will receive health information over the duration of the study (48-weeks) covering health issues such as mental health wellbeing, healthy eating and developing good sleeping habits. Control group participants will be given no instruction on physical activity during the study, after which they also receive the walking kit. Control group participants will be sent a control group study kit consisting of a falls calendar and printed material on a health topic. Information on a new health topic will be mailed out at 12-weeks and 24-weeks in parallel with the intervention group. (See Figure 2)

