#### Outcome measures

The main outcome measure is falls over the 12-month study period. A fall is defined as *'Unintentionally coming to rest on the ground, floor, or other lower level' *[27,28]. Falls will be recorded on a falls calendar, a method used successfully in previous falls prevention studies [27]. Each fall will be followed up with a telephone call by a research assistant to confirm the fall and to ascertain the circumstances around the fall including whether the fall resulted in any injuries, what treatment was sought.

Secondary outcome measures include:

• Dynamic balance and strength (sub-sample only)

• Physical performance (sub-sample only)

• Quality of life

• Walking behaviour

Other measures will be collected through the initial screening and baseline questionnaire and include basic demographic information, falls history, falls efficacy, self-reported levels of physical activity, walking self-efficacy and perceived neighbourhood walkability.

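### Only the walking arm logs its walks on the falls calendar, so the primary-outcome instrument is used differently by arm and can show allocation; the rate ratio may be biased in an unknown direction.

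*Protocol article*

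**What the plan says.** Outcome measures, in the protocol article, defines the endpoint and its instrument: "The main outcome measure is falls over the 12-month study period", and "Falls will be recorded on a falls calendar, a method used successfully in previous falls prevention studies". It then adds a confirmation step: "Each fall will be followed up with a telephone call by a research assistant to confirm the fall". The same call collects the circumstances of the fall, any injury and any treatment.

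The Intervention section (the text after Figure 2) gives the calendar a further job in one arm: "Intervention group participants will record the duration and frequency of walking, on their falls calendar". For the other arm it says: "Control group participants will be sent a control group study kit consisting of a falls calendar and printed material on a health topic". It also says: "Control group participants will be given no instruction on physical activity during the study". No walking record or other routine entry is described for controls.

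On masking, Recruitment and randomization says: "Participants will obviously not be blinded to group allocation". For staff, it says that there will be no information about individual "group allocation revealed to research assistants during the follow-up interview until the last set of questions", which deal with evaluation of the program. Nothing comparable is said about handling calendars or about the calls that confirm falls.

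The Analysis section compares falls between arms by negative binomial regression under intention to treat. It also plans a dose-response analysis of walking and falls within the intervention group.

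**The concern.** An unblinded trial with a self-reported endpoint depends on both arms recording that endpoint in the same way. Here one arm has a recurring reason to pick up the form and the other has none described. The Intervention section also lists keeping a record of walks or steps under self-regulation, one of the constructs targeted by the manuals and telephone support, so logging is part of what the walking arm is encouraged to do.

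Two consequences follow.

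- **Completeness.** A walker who opens the calendar to log a walk is prompted to note a fall. That could raise the walking arm's count relative to controls. Equally, the burden of logging, or knowledge of allocation, could lower it.
- **Masking.** A calendar with walking entries shows the arm to whoever reads it. If that person also makes the confirmation call, the decision on whether an event counts is no longer masked.

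The regression cannot separate a difference in recording from a difference in falling, and a larger sample does not help. The stakes are high because the Discussion treats both a benefit and a possible harm of walking as conclusions with public health consequences. Either could be weakened or mimicked by unequal recording.

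**Working it through.** **1. The passages side by side**

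| Feature | Walking arm | Control arm |
|---|---|---|
| Instrument for falls | Falls calendar | Falls calendar |
| Other entries on it | Walking duration and frequency | None described |
| Instruction on physical activity | Progressive walking program | None during the study |
| Participant masked | No | No |
| Staff masking at follow-up interview | Stated, up to the last questions | Same |
| Staff masking at fall confirmation | Not stated | Not stated |

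The second row is a difference set by a stated rule. It is not a detail left out of a condensed article.

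**2. Effect on the rate ratio**

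Let c_I and c_C be the shares of true falls captured in the intervention and control arms. Each recorded rate is the true rate times its capture share, so

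observed ratio = true ratio × (c_I / c_C).

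The protocol gives no capture shares. The ratios below are assumptions, shown in both directions. The 0.65 is the effect in the Sample size section.

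| Assumed c_I / c_C | True 0.65 observed as | True 1.00 observed as |
|---|---|---|
| 0.80 | 0.65 × 0.80 = 0.52 | 0.80 |
| 0.90 | 0.65 × 0.90 = 0.585 | 0.90 |
| 0.95 | 0.65 × 0.95 = 0.6175 | 0.95 |
| 1.00 | 0.65 | 1.00 |
| 1.05 | 0.65 × 1.05 = 0.6825 (0.68) | 1.05 |
| 1.10 | 0.65 × 1.10 = 0.715 (0.72) | 1.10 |
| 1.25 | 0.65 × 1.25 = 0.8125 (0.81) | 1.25 |

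Sample size does not enter the formula, so recruiting more people leaves the shift unchanged.

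**3. The same ratios on the protocol's own power basis**

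Inputs from Sample size: 33% of controls fall at least once, RR 0.65, alpha 0.05, power 80%. Two-sided testing is assumed, since sidedness is not stated.

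- p1 = 0.33; p2 = 0.33 × 0.65 = 0.2145; difference = 0.1155; mean = 0.27225.
- n = [1.960 × √(2 × 0.27225 × 0.72775) + 0.842 × √(0.33 × 0.67 + 0.2145 × 0.7855)]² / 0.1155² = 232 per group, which is the stated figure.

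Holding 232 per group and 33% recorded fallers among controls, and multiplying the walking arm's proportion by the assumed ratio:

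- With a true 0.65, power goes from 80% to 71% (ratio 1.05), 61% (1.10) or 31% (1.25).
- With no true effect, the chance of a falsely significant benefit goes from the nominal 2.5% to 5.7% (0.95), 11.6% (0.90) or 34% (0.80).

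This step is rough. It applies a capture ratio for falls to the proportion of fallers, while the planned analysis models counts. It shows scale only.

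**The case against.** The strongest reply is that nothing here is an error or a contradiction. Putting a log on a calendar that participants already hold is a low-burden choice, the calendar method has been used before, and how calendars are returned and who handles them are operational details that an article commonly leaves to the full protocol. That stands as far as it goes. Silence on calendar handling is not itself the finding; the finding is the stated one-arm use of the outcome form.

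Three stronger readings are tempting, and the document does not support them.

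- *Controls write on the calendar only when they fall.* The protocol does not say so. They may mark every day, return it on a schedule or get reminders. If both arms complete and return it regularly, much of the possible recording gap would close.
- *The staff who confirm falls see the walking entries.* The protocol says only that a research assistant telephones. Sight of the calendar is a plausible inference, not a stated fact.
- *The rate ratio is biased, and against walking.* The text supports a risk only. Prompting would push the ratio up; logging burden or knowledge of allocation could push it down.

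It is also fair to object that a separate sheet leaves other routes open. Participants know their arm, the walking arm gets repeated telephone counseling, and questions about how a fall happened may reveal a walking program. This is correct and limits what the fix can achieve.

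**Conclusion.** The point holds as a risk built into the design. By a stated rule, the primary-outcome form has a second, recurring use in the walking arm alone. Falls may therefore be recorded with different completeness by arm, and a completed calendar identifies the arm to its reader. The one staff-masking statement does not reach the confirmation of falls.

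The size and direction of any bias cannot be derived from the document. The range in the working rests entirely on assumed capture ratios: 1.05 to 1.25 would turn a true 0.65 into 0.68 to 0.81 and a true 1.00 into 1.05 to 1.25, and ratios below 1 would exaggerate benefit. No specific loss of power should be charged to the calendar, because power under the planned model also depends on the fall rate, the overdispersion and the number evaluable.

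The change is worth making because it is cheap and because the planned analysis cannot correct unequal recording afterwards.

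**What to change.** - Give both arms an identical calendar that records falls only, with the same instructions, completion routine and return schedule.
- Move the walking record to a separate sheet in the intervention kit, returned to the coaching staff and not with the calendar.
- Have the research assistants who confirm falls work from the falls calendar and a fixed script, without access to the walking log, and extend the masking statement in Recruitment and randomization to cover these calls.

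The cost is one extra printed sheet, a rule for sorting mail, slightly more work for walking-arm participants and possibly fewer walking logs for the dose-response analysis. The change reduces unmasking without removing it, since participants know their allocation and may disclose it on the call.

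### Only the walking arm logs walks on the falls calendar and is coached by telephone, which creates a risk of unequal fall reporting between the arms

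*Protocol article*

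**What the plan says.** All of this is in the Protocol article.

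- **Outcome (Outcome measures).** "The main outcome measure is falls over the 12-month study period". On ascertainment: "Falls will be recorded on a falls calendar, a method used successfully in previous falls prevention studies". On confirmation: "Each fall will be followed up with a telephone call by a research assistant to confirm the fall". No difference by arm is stated for either step.
- **Blinding (Recruitment and randomization).** Participants know their group. Research assistants are kept unaware of it in the follow-up interview until the closing questions on programme evaluation.
- **Walking arm (Intervention).** Manuals and telephone coaching span 48 weeks in three phases, and "The third phase (weeks 25-48) is the maintenance phase". On the calls: "Participants receive telephone counseling at the beginning and mid-point for each phase of the program; a total of eight calls". The behavioural aims of the manuals and the telephone support include keeping a record of walks or steps. That record sits on the outcome instrument: "Intervention group participants will record the duration and frequency of walking, on their falls calendar".
- **Control arm (Intervention, text after Figure 2).** Controls are sent a falls calendar and a first health topic. After that: "Information on a new health topic will be mailed out at 12-weeks and 24-weeks in parallel with the intervention group". No calls to controls are described. The same paragraph says that control information covers the full 48 weeks.
- **Analysis.** Intention to treat, with negative binomial regression of falls at 48 weeks.

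**The concern.** A fall counts only if the participant writes it down and the calendar reaches the study. The confirmation call can remove a false report, but it cannot recover a fall that was never recorded. How regularly the calendar is used therefore affects the primary outcome directly.

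The plan makes that regularity differ by arm. A walker opens the calendar to log each walk, and the coaching encourages such record keeping. A control has no reason to open it except a fall, and no call is described that would bring it to mind. A coach need not mention falls for the walkers' calendars to be better kept.

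If control falls are recorded less completely, the observed ratio of walking to control fall rates rises. A true benefit is diluted, and a programme with no effect looks harmful. The second error matters here. The Background treats greater exposure to falls through walking as a real possibility, and the abstract's Discussion says that prevention resources should go elsewhere if walking does not help or does harm. Neither intention to treat nor the negative binomial model corrects for falls missing from one arm. Keeping interviewers unaware of allocation does not help either, because falls come from the calendar.

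**Working it through.** **1. Contacts set side by side**

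| | Walking arm | Control arm |
|---|---|---|
| Falls calendar | yes | yes |
| Other regular use of that calendar | walk duration and frequency | none described |
| Printed material | three manuals, one per phase | start, week 12, week 24 |
| Telephone calls | start and mid-point of each phase | none described |

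The print schedules match. The differences are the walk log and the calls.

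**2. Number and timing of calls**

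By the phase rule: 3 phases × 2 calls = 6. The article states eight, so two calls have no stated time, and the rule and the total need to be reconciled. With phases at weeks 1–12, 13–24 and 25–48, the six calls fall at about weeks 1, 6–7, 13, 18–19, 25 and 36–37. That is four calls against none up to week 24, and two against none afterwards (up to four if both unplaced calls fall there). The imbalance runs from the start, and the last call placed by the rule is at about week 36–37.

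**3. Possible size**

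The article gives no reporting rates, so q and f below are assumptions. Let q be the share of control falls missed beyond any share missed by walkers, and f the part of follow-up in which this happens, with falls spread evenly over time:

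observed ratio = true ratio ÷ (1 − f·q)

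| f | q | divisor | true 1.00 seen as | true 0.65 seen as |
|---|---|---|---|---|
| 0.5 | 0.10 | 0.95 | 1.05 | 0.68 |
| 0.5 | 0.20 | 0.90 | 1.11 | 0.72 |
| 1.0 | 0.10 | 0.90 | 1.11 | 0.72 |
| 1.0 | 0.20 | 0.80 | 1.25 | 0.81 |

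The ratio 0.65 is the target effect under Sample size. If walkers under-report instead, the ratio is multiplied by (1 − f·q): at f = 0.5 and q = 0.10 or 0.20, a true 1.00 is seen as 0.95 or 0.90. Equal reporting gives no shift.

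**4. Why no power loss is quoted**

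The plan's 232 per group reproduces as a two-sided comparison of proportions, 0.33 against 0.33 × 0.65 = 0.2145, with mean 0.27225:

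n = [1.96·√(2 × 0.27225 × 0.72775) + 0.8416·√(0.33 × 0.67 + 0.2145 × 0.7855)]² ÷ 0.1155² = 232

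That calculation concerns the proportion who fall at all. The shift in step 3 concerns the number of falls. A repeat faller who omits one fall is still a faller, and the planned analysis is a count model. Applying q to the 33% would overstate the loss.

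**The case against.** The strongest reply has four parts.

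- **The mailings are not the problem.** Three control packs parallel three walking manuals, and the pack at week 24 can be read as serving weeks 25–48, as the last manual does. This stands. A reader might infer that the arms diverge at week 24, when dated control contact ends, and that half of follow-up is affected. The article does not support that: the calls and the walk log differ from the beginning, and week 24 is only the last dated mailing. Figure 2, which may show more of the schedule, is not available.
- **Prompting of fall reports is inferred.** The listed coaching content does not include asking about falls, and nothing makes a coach a source of fall data. This also stands, so it cannot be said that falls mentioned to coaches are counted. The walk log does not depend on that inference, because its place on the falls calendar is stated.
- **Calendar return and reminders may be set out in the full protocol.** Their absence from an article is no fault. If they are identical by arm, the risk shrinks. The second use of the calendar by one arm would remain.
- **Extra contact is part of the intervention.** This is true, and the coaching need not change. The issue is only its link to fall recording.

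**Conclusion.** The point holds as a risk of differential ascertainment in the primary outcome. It rests on four stated facts: self-recorded falls, unblinded participants, walks logged on the falls calendar in one arm only, and telephone support in that arm that promotes such logging. With no calls to controls described, the reinforcement is one-sided.

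A reader might go further and conclude that the rate ratio is biased against walking. The article does not show that. It fixes neither size nor direction, although better-kept calendars among walkers is the more plausible case. A shift of about 5% to 11% follows only if controls miss an extra 10% to 20% of their falls over half of follow-up. Both the gap and the half are assumptions. A gap lasting throughout would roughly double the shift, equal reporting would remove it, and under-reporting by walkers would reverse it.

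The change is worth making because it is cheap and no planned analysis can repair the problem afterwards.

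**What to change.** 1. Record walks on a form separate from the falls calendar, so that the calendar serves the same purpose in both arms.
2. State that falls enter the primary analysis only from the calendar and the confirmation call it triggers.
3. Use the same calendar return interval and the same non-return reminder in both arms, run by staff not involved in coaching. If the full protocol already provides this, a sentence saying so is enough.
4. Instruct coaching callers neither to ask about falls nor to prompt the falls calendar.
5. Report calendar return by arm, so that readers can judge whether ascertainment was balanced.

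A later control mailing would fit the statement that control information runs over 48 weeks. It is optional and would not by itself balance six to eight calls.

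The cost is one extra form for walkers, a line in the coaching script and a line in the outcome definition. A few falls mentioned only to coaches would go uncounted. The walking data needed for the planned dose-response analysis are kept, on the separate form.
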